## Abstract

**Objective:**

Most people with epilepsy (PWE) could live seizure‐free if treated with one or more antiseizure medications (ASMs). The World Health Organization (WHO) estimates that 75% of PWE in low‐resource settings lack adequate antiseizure treatment. Limited education surrounding epilepsy and the out‐of‐pocket costs of ASMs in particular pose barriers to managing epilepsy in resource‐poor, low‐income settings. The aim of this study is to implement and test a novel strategy to improve outcomes across the epilepsy care cascade marked by (1) retention in epilepsy care, (2) adherence to ASMs, and (3) seizure reduction, with the measured goal of seizure freedom.

**Methods:**

A randomized, double‐blinded clinical trial will be performed, centered at the Ignace Deen Hospital in Conakry, Republic of Guinea, in Western Sub‐Saharan Africa. Two hundred people with clinically diagnosed epilepsy, ages 18 years and above, will receive education on epilepsy and then be randomized to (i) free ASMs versus (ii) conditional cash, conditioned upon return to the epilepsy clinic. Participants will be followed for 360 days with study visits every 90 days following enrollment.

**Significance:**

We design a randomized trial for PWE in Guinea, a low‐resource setting with a high proportion of untreated PWE and a nearly completely privatized healthcare system. The trial includes a conditional cash transfer intervention, which has yet to be tested as a targeted means to improve outcomes for people with a chronic neurological disorder. The trial aims to provide an evidence base for the treatment of epilepsy in such settings.

**Plain Language Summary:**

We present a clinical trial protocol for a randomized, blinded study of 200 people with epilepsy in the low‐resource African Republic of Guinea, providing an educational intervention (*E*), and then randomizing in a 1:1 allocation to either free antiseizure medication (*m*) or conditional cash (*c*
^2^) for 360 days. Measured outcomes include (1) returning to outpatient epilepsy care, (2) adherence to antiseizure medications (ASMs), and (3) reducing the number of seizures. This study is an initial look at giving small amounts of cash for desired results (or “nudges”) for improving epilepsy outcomes in the sub‐Saharan African and brain disorder contexts.

Key points
Untreated epilepsy remains an important public health problem in resource‐limited settings such as the Republic of Guinea.There have yet to be clinical trials that evaluate the role of conditional cash in treating epilepsy.We provide a clinical trial protocol to test conditional cash versus free antiseizure medications (ASMs) in Guinea.Measured outcomes will include whether participants return to outpatient epilepsy care, adhere to ASMs, and have fewer seizures.This trial could provide evidence for the role of conditional cash for untreated people with epilepsy in resource‐limited settings.

## INTRODUCTION

1

Epilepsy, the tendency to recurrent unprovoked seizures,^1^ is a chronic neurological disorder that presents across the lifespan and affects approximately 2% of the sub‐Saharan African population.^2^ Although epilepsy is usually treatable with one or more antiseizure medications (ASMs), a significant number of people with epilepsy (PWE) in low‐resource settings do not have access to or do not regularly take ASMs.^2^ Multiple organizations and investigators have noted the *epilepsy treatment gap*—defined as the difference between the number of PWE who have active epilepsy treated with ASMs versus not or the proportion of people that should be treated for epilepsy yet are not—but few studies provide an evidence base on how to change the current situation.^3^, ^4^, ^5^, ^6^ Most recently, the World Health Assembly adopted the *Intersectoral Global Action Plan on Epilepsy and Other Neurological Disorders* (“Draft Intersectoral global action plan on epilepsy and other neurological disorders 2022–2031,”^7^). This includes targets to treat more people with neurological disorders with essential medicines including ASMs for PWE.

Cascades of care are being developed to assess the delivery of care for noncommunicable diseases, similar to the approach seen in HIV/AIDS.^8^ In a cascade, specific targets are identified including: (1) ensuring >90% of PWE are aware of the diagnosis as a brain disorder, (2) retaining >90% of PWE in epilepsy care, (3) ensuring >80% of PWE take quality, appropriate chosen and dosed ASMs, and (4) ensuring seizure freedom in 70% of people treated.^9^ Of these, seizure freedom (step four) is the outcome most valued by PWE and is associated with a self‐reported quality of life equivalent to people without epilepsy. Given the high efficacy of ASMs, access to ASMs would lead to seizure freedom in a majority of PWE.

Access to ASMs remains a challenge to seizure prevention and epilepsy treatment in low‐resource settings. Epilepsy care in the Republic of Guinea, a low‐income country in Western Sub‐Saharan Africa with a 2020 gross national income of 1020 USD per capita,^10^ reflects a low‐functioning health system with few epilepsy‐trained clinicians, and high volumes of patients. Guinea has few health facilities and a nearly completely privatized healthcare system, necessitating costs to be paid “out of pocket.” PWE often go without ASMs due to multiple factors at the level of the patient, provider, and health system.

The Guinea Epilepsy Project, a prospective observational cohort study, began in 2017 by the Guinean and U.S. neurologist authors, has enrolled several 100 PWE to date.^11^, ^12^, ^13^, ^14^, ^15^ Several negative consequences of untreated and undertreated epilepsy have been observed including unintentional death; missed opportunities for school attendance of Guinean children with epilepsy^12^; poor cognitive performance; frequent unintentional injuries; epilepsy stigma^16^; high rates of traditional healing injuries including cuttings, instrumentation, and animal sacrifices^11^; and large losses of personal wealth on ineffective treatment options.^17^ Similar to other low‐resource locations, a high number of PWE do not take ASMs and have suffered serious consequences as a result, including death from unintentional injury or status epilepticus.^13^

As a response to this tragic situation, the study team proposes to compare two ways to deliver epilepsy care to people with epilepsy (PWE) in a low‐income setting. Although several lines of evidence suggest that both these interventions will lead to improved outcomes,^18^, ^19^, ^20^ they have not been directly tested in low‐resource populations with low literacy. *Conditional cash transfer* (CCT) interventions in particular have not been systematically tested in PWE or in people with any chronic neurological disorder. CCT interventions grant individuals a sum of money on the condition that they fulfill a predetermined task. In this way, CCT interventions create a “nudge,” or an economic incentive, for taking a desired course of action. These interventions differ notably from *unconditional cash transfer* (UCT) interventions, which simply provide direct payment to individuals without any behavioral nudges. As such, CCT interventions uniquely serve as an important lever for both alleviating the financial burden of poverty and incentivizing people to act for the benefit of their own health.

A global scoping review of randomized trials with health‐focused CCT interventions found most CCT interventions benefit health outcomes and have the potential to change patient behaviors for a range of disease areas.^21^ However, CCT interventions are yet to be tested for neurological conditions. Moreover, CCT has limited testing for health outcomes in West African countries, such as Guinea, where traditional healing, high stigma, poverty, and misbeliefs about the origins of epilepsy prevail.^22^, ^23^, ^24^, ^25^ CCT interventions could therefore enable epilepsy patients to break out of a cycle of poverty that can accompany high seizure burdens and resultantly, an inability to attend school or work.

### Trial design

1.1

A randomized, double‐blinded clinical trial will be performed, including multiple healthcare facility sites in rural and urban Guinea but headquartered at the Ignace Deen Hospital in the capital city, Conakry. Two hundred PWE, clinically diagnosed by a Guinean and a U.S. neurologist, ages 18 years and above, will be enrolled and randomized 1:1 to (i) education and medication, or (ii) education and CCT (Figure 1). All participants will receive epilepsy education. Participants will be interviewed and examined by the Guinean–U.S. study team of neurologists at each visit. Follow‐up visits every 90 days until day 360 (approximately 1 calendar year) will assess the intervention on participants' clinical and socioeconomic outcomes. The recurring 90‐day follow‐up visits are considered beneficial to participants who may not access epilepsy care in any other way while also providing a sufficiently long timeline to study the sustainability of this intervention.

**FIGURE 1 epi412889-fig-0001:**
[figure not shown]
Study enrollment and intervention randomization flow diagram.

### Objectives

1.2

The primary objective is to implement and test a novel strategy to improve outcomes across the epilepsy care cascade marked by (1) retention in epilepsy care, (2) adherence to ASMs, and (3) seizure reduction with the measured goal of seizure freedom.

The first aim is to compare free ASMs vs. conditional cash using the epilepsy cascade of care. We hypothesize that the provision of free medication versus conditional cash will lead to (1) similar retention in epilepsy care—90% of PWE—at 360 days (Hypothesis 1a), (2) 80% of PWE regularly taking ASMs at 360 days (Hypothesis 1b), and (3) 65% of PWE achieving seizure freedom 360 days postenrollment (Hypothesis 1c).

The secondary aim is to detail facilitators and barriers to free medication versus conditional cash to improve seizure freedom among PWE. We hypothesize that barriers and facilitators to the uptake of each intervention strategy can be learned through careful, structured documentation by healthcare workers during study visits using an investigator‐designed written intake form as well as free‐text responses, serving as foundational information for a future larger‐scale implementation study in low‐resource populations.

## METHODS: PARTICIPANTS, INTERVENTIONS, AND OUTCOMES

2

Institutional Review Board approval will be obtained through the Ignace Deen Hospital in Guinea and the U.S. study team's institution.

### Study setting

2.1

The Ignace Deen Hospital is one of two teaching hospitals in Conakry, receiving several thousand cases of epilepsy per year. Additional recruitment and enrollment are planned to occur in Kankan, Forecariah, and Dubreka regional health facilities. There are five practicing neurologists in Guinea. Table 1 displays summary statistics from a prior cohort study we conducted with 297 Guinean PWE whose characteristics are expected to resemble future trial participants.

**TABLE 1 epi412889-tbl-0001:** Epilepsy patients, Republic of Guinea (*n* = 297).

	Female (*n* = 159)	Male (*n* = 138)	Children (<18 years, *n* = 148)	Adults (> = 18 years, *n* = 149)	Full cohort (*n* = 297)
Mean age (years; range)	20.4 (1–66)	18.6 (0.8–62)	8.5 (0–17)	30.5 (18–66)	19.6 (0.8–66)
Highest education (*n*)					
No school	35	32	48	19	67
Primary school	52	50	72	30	102
Middle school	23	21	18	26	44
High school	17	17	5	29	34
University	30	15	1	44	45
Was water unavailable for at least 1 day in the past 2 weeks? (% yes)	47	37	40	44	43
Has previously taken ASMs (% yes)	89	78	84	84	84
Currently taking ASMs (% yes)	70	54	60	65	63
Annual mean household income per capita (USD)	639	924	603	975	770
Duration of epilepsy, years (mean)	7.6	7.2	3.5	11.1	7.4
Seizure frequency in past month (mean)	3.0	4.1	4.1	2.8	3.5
Ever injured due to seizures (% yes)	58	51	35	74	55
Ever used non‐allopathic treatments (*n*)					
Traditional medicine	92	70	78	84	162
Prayer	29	26	29	26	55
Special diets	16	3	4	15	19
ASMs ever taken (*n*)					
Carbamazepine	70	51	44	77	121
Benzodiazepine	6	7	6	7	13
Levetiracetam	28	19	29	18	47
Phenobarbital	60	33	41	52	93
Phenytoin	0	1	0	1	1
Sodium valproate	58	35	58	35	93
Other ASM	10	11	5	16	21
Previous brain imaging (% yes)					
CT	42	33	37	38	38
EEG	49	49	55	42	49
MRI	5	2	4	3	4

*Note*: Gray shades denote the title of the columns.

### Eligibility criteria

2.2

PWE will be screened in person and enrolled on a “first come, first served” basis. The goal is to enroll a person with active epilepsy. The person will have therefore experienced two or more recurrent, unprovoked seizures in the past year (inclusion criterion) and not have had any other diagnosis that can better explain the symptoms, as evaluated by the study neurologists (one Guinean and one U.S.). Specifically, patients with exclusively febrile seizures, pseudo‐seizures, and other movement disorders or episodic events that are not primary epilepsy are not eligible. The study will include a brain MRI such that secondary seizures from a space‐occupying lesion (secondary to tumor, stroke) can be detected and referred to usual care but not enrolled. Similarly, seizures that are provoked (e.g., alcohol withdrawal) will be queried through the intake forms and corroborated by physical examination and extant medical records.

Inclusion criteria are (1) resident of Guinea, 18 years or older, presenting to one of the study sites in Guinea; (2) able to provide informed consent or have a next of kin proxy provide informed consent when appropriate; (3) experienced two or more recurrent, unprovoked seizures in the past year; (4) able to provide a clinical history or have a next of kin provide it; (5) not taking a daily ASM for epilepsy for the past 30 days or more for any reason; (6) willing to have his/her data sent anonymously to the U.S. study site; and (7) anticipated to be able to return for follow‐up visits for 360 days.

Exclusion criteria are (1) any other diagnosis that can better explain the symptoms, making the diagnosis of primary, active epilepsy unlikely; (2) unable to undergo the study procedures; (3) age less than 18 years old due to the need to measure several self‐reported outcomes; (4) unable to provide informed consent (or have an appropriate proxy informed consent); (5) currently pregnant or lactating; (6) secondary seizures, for example, due to a condition that requires imminent treatment (e.g., malignancy, alcohol withdrawal); (7) critically ill; (8) exclusively pseudo‐seizures/nonepileptic behavioral events; (9) unwilling to take an ASMs for epilepsy; (10) already treated with ASMs for other purposes (e.g., mood, pain); (11) known to be unable to return for follow‐up visits.

The investigators will monitor participants' health throughout the study and re‐evaluate eligibility. For example, a woman may become pregnant or a participant may have a new illness (e.g., malaria). It will be ensured that all pregnant women have access to clinical care and an ASM (such as levetiracetam or lamotrigine) that is associated with the lowest fetal risk (whether she remains in the study or is withdrawn). Changes in health status and medical risk will be recorded, and the study team will adjudicate the event for administrative withdrawal of the participant. All withdrawn participants will have access to usual care following study discontinuation.

### Informed consent

2.3

Screening will be performed by Guinean investigators with mentorship and collaboration with the U.S. team (Appendix S1) and will include a brain MRI to rule out other diagnoses (e.g., tumors, untreated significant hydrocephalus). An estimated 50% of the enrollment will occur in Conakry and 50% at rural and peri‐urban sites.

## INTERVENTIONS

3

### Explanation for the choice of comparators

3.1

Participants randomized to the CCT arm will still be given an ASM recommendation and advice on purchasing ASMs consistent with the best available neurological care. The decision to create two arms will enable the study team to assess the effectiveness of each intervention without using a noninterventional control group. Using a control group comparator without any intervention was considered unethical. All participants will have access to local diagnostic testing as needed.

### Intervention description

3.2

The education intervention will be given to each participant upon study enrollment in the form of a prerecorded, standardized video, made by the investigators, lasting approximately 30 min. The video is designed for people with low literacy and will answer the following basic questions: [What is a seizure? What is epilepsy? Why does epilepsy occur? Why is epilepsy a brain disorder? What works to treat epilepsy? What does not work to treat epilepsy? Why are ASMs important?] The video will be available in local languages (Sousou and Malinké), English, and French and shown on electronic tablets. A question‐and‐answer period, led by the study neurologists, will follow with no limitations on the amount of time. A flyer providing basic, written information on the education intervention will be given.

ASMs will be provided free of charge and prescribed for the participants in the study arm that includes the medication intervention. The ASM choice will be determined at the discretion of the neurologist in the context of the patient's history. There is no one best ASM for all patients, and most ASMs provide similar efficacy but dissimilar side effects and safety. There will be a total of seven possible ASMs to be used.

CCT will be conditioned on the return for follow‐up visits to the outpatient epilepsy clinic for scheduled appointments (±7 days every 90 days). Each visit for those in the CCT groups will entail the provision of 15 USD (given in the equivalent of Guinean Francs) to participants. This amount is anticipated to be a “nudge” (i.e., mildly incentivizing) as it exceeds the general cost of transportation for a return visit in the area (~5 USD on average) and ASM (which approximately costs ~4–10 USD for a monthly dosage in Guinea).^11^ It is important to note that this nudge will ensure participants in the CCT arm can afford the ASM, which enables study staff to assess outcomes from behavioral change rather than affordability considerations. The transfer will also be conditional on presence at visits, not on seizure outcomes. This ensures that participants are not penalized for aspects of their illness that are beyond their control.

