### Who will be blinded?

4.1

Participants will be blinded to the primary study hypothesis. The Guinean site collaborators providing the intervention will be blinded to the primary study hypothesis.

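### Nothing places the ASM choice before allocation: the drug may then depend on the arm, seizure and ASM-use differences cannot be read as behaviour alone, and adjusting for ASM type can bias the arm comparison

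*Protocol article*

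**What the plan says.** On drug choice, section 3.2 (Intervention description) states "The ASM choice will be determined at the discretion of the neurologist in the context of the patient's history". It adds "There will be a total of seven possible ASMs to be used" and that "most ASMs provide similar efficacy but dissimilar side effects and safety".

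On supply, the arms differ. Section 3.2: "ASMs will be provided free of charge and prescribed for the participants in the study arm that includes the medication intervention". Section 3.1 (Explanation for the choice of comparators): "Participants randomized to the CCT arm will still be given an ASM recommendation and advice on purchasing ASMs".

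On blinding, section 4.1 says "The Guinean site collaborators providing the intervention will be blinded to the primary study hypothesis". Participants are blinded in the same sense. No blinding to the arm itself is described there.

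On money, section 3.2 says "Each visit for those in the CCT groups will entail the provision of 15 USD", puts transport for a return visit at about 5 USD, and gives the price of ASMs: "which approximately costs ~4–10 USD for a monthly dosage in Guinea". It concludes that the payment makes the drug affordable in the cash arm, so that outcomes can be read as changes in behaviour and not as effects of ability to pay.

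On analysis, section 6 adjusts the two-arm retention comparison for the type of medication. It also lists ASM type among the baseline variables of the longitudinal mixed model. The two-sample tests for Hypothesis 1b (regular ASM use) and 1c (seizure freedom) carry no stated adjustment.

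**The concern.** The person who picks the drug is free to use judgement, is not described as blinded to the arm, and in one arm only has to think about what the patient can pay for. If the choice follows allocation, the drugs recommended can differ between arms. Two things are then at stake.

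The first is interpretation. A difference in continued ASM use or seizure freedom would combine the participant's response to cash or free supply with the prescriber's response to the arm. Section 3.2 invites the reader to see only the participant's behaviour.

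The second is analysis, and it reaches the primary hypothesis. An adjustment for ASM type is harmless if the variable is fixed before randomisation. If allocation can influence it, the adjusted arm comparison is no longer protected by randomisation.

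**Working it through.** **1. The plan's own figures.** Section 6 sizes the trial on retention: 90% rate, 80% power, and a Bonferroni split of 0.05 over two tests, read here as one-sided 0.025 each (the sidedness is inferred from the non-inferiority tests).

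- One-sample, margin 8.5 points: 0.90 × 0.10 × (1.960 + 0.842)² / 0.085² = 97.8, so 98, as stated.
- Two-sample, margin 12 points, with 90% also assumed in the free-ASM arm: 2 × 0.90 × 0.10 × (1.960 + 0.842)² / 0.12² = 98.1, so 99, as stated.

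Neither formula involves ASM type, so the sample size is not in question here.

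**2. Order of choice and allocation.** The Abstract puts education before randomisation. No sentence does the same for the drug choice. Section 3.1 speaks of the recommendation going to people already randomised to cash, and whoever advises on buying the drug must know the arm. Choice after allocation is therefore the natural reading, but it is not stated.

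**3. Is there a price reason for the drug to differ?** With 30-day months, from section 3.2:

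- ASM for 90 days: 3 × 4 = 12 USD to 3 × 10 = 30 USD.
- With one return trip: 12 + 5 = 17 USD to 30 + 5 = 35 USD, against a payment of 15 USD.
- Left after transport: 15 − 5 = 10 USD, or 10 / 3 = 3.33 USD a month, below the lowest quoted price of 4 USD.

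Section 3.2 ties the cash to follow-up visits, but Table 3 also marks a cash allocation at baseline. On that count, five payments give 5 × 15 = 75 USD. Against this stand 12 × 4 = 48 to 12 × 10 = 120 USD of ASM plus 4 × 5 = 20 USD of travel, 68 to 140 USD in all. Only the cheap end is covered, and only if the day-360 payment is included; the four earlier payments give 60 USD. On either count price can bear on the drug in the cash arm, and in that arm only.

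**4. What the adjustment would do.** Eligibility requires no daily ASM for at least 30 days, so ASM type cannot be a treatment in use at enrolment. Unless it means a drug taken in the past, it is the drug chosen in the trial. Suppose poorer or more distant cash-arm patients are steered to cheaper drugs. Then cash-arm patients on a cheap drug include people whose free-arm counterparts are on another drug. Comparing arms within drug type sets unlike groups against each other. It also removes any part of the arm effect that runs through the drug.

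**5. Illustration for seizure freedom.** All inputs except the 65% rate and 100 per arm are assumptions. If a share s of one arm receives a drug whose seizure-freedom rate differs by g, the arm difference is d = s × g. With SE = √[0.65 × 0.35/100 + (0.65 + d)(0.35 − d)/100], the chance of rejection at one-sided 0.05 is 1 − Φ(1.645 − d/SE).

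| s | g | d | rejection |
|---|---|---|---|
| any | 0 | 0 | 5% |
| 0.2 | 0.05 | 1 point | 6.7% |
| 0.2 | 0.10 | 2 points | 8.9% |
| 0.4 | 0.10 | 4 points | 14.9% |
| 0.6 | 0.20 | 12 points | 59.5% |

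These are for a shift in favour of the cash arm. A shift against it would push rejection of the 1c null below 5%.

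**The case against.** The strongest reply is that the trial compares two ways of delivering care, as the Introduction puts it. If buying one's own drug leads to a different drug, that is a consequence of the strategy, not confounding. This stands. A reader might infer that the seizure comparison is invalid; the documents do not support that, because randomisation protects the comparison of strategies.

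Second, a reader might infer that the drug is definitely chosen after the arm is known. That is not stated. The article is condensed, the full protocol may fix the order, and calling ASM type a baseline variable points the other way. The design is also called double-blinded, and the Discussion mentions blindness to allocation. Yet section 4.1 names only the hypothesis, and purchasing advice cannot be given without knowing the arm.

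Third, ASM type is not ignored, so it would be wrong to say the plan has no answer to a difference in drugs. But the planned answer works only if the variable precedes allocation.

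Fourth, section 3.2 calls most ASMs similar in efficacy, which limits the effect on seizures. This stands too. The same sentence says side effects and safety differ, which could still affect continued use under Hypothesis 1b.

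Finally, a reader might infer that the cash arm may draw on different drugs from the seven listed. The sentence about seven ASMs is not limited to either arm, so this is unclear rather than shown.

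**Conclusion.** The point holds in limited form. As written, the recommended drug may depend on the arm, since the choice is discretionary, the prescriber is not described as blinded to allocation, supply differs, and no order is fixed. The strategy comparison survives. Attribution of differences in ASM use or seizure freedom to behaviour alone does not. The adjustment for ASM type in section 6 is sound only if the drug is fixed before allocation; otherwise it can bias the retention comparison and the mixed model.

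The size cannot be derived from the documents. For seizure freedom it is zero if the drugs are equally effective; the 2 to 4 points above rest wholly on assumed shares and an assumed 10-point difference between drugs. The direct effect of drug choice on attendance, the primary outcome, is not shown; there the exposure is through the adjustment.

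Separately, the statement that the payment makes the drug affordable conflicts with the article's own prices for most of the range, and the two must be reconciled.

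**What to change.** - In sections 3.1 and 3.2, state that at the baseline visit the neurologist records the intended ASM for every participant before the allocation is revealed. The step fits between the education session and randomisation.
- In section 6, use that recorded value, not the ASM actually taken, wherever medication type or ASM type is adjusted for.
- Report intended against actual ASM by arm, with the reason for any difference.
- State whether the list of seven applies to both arms, and that the seizure and ASM-use comparisons estimate the effect of the whole strategy.
- Reconcile the affordability statement in section 3.2 with its cost figures, and the timing of the cash in section 3.2 with the baseline entry in Table 3.

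Drug choice and later changes remain with the neurologist; the request concerns timing and documentation only. The cost is one form field and a fixed order of two steps at one visit. In some participants the recorded and actual drug will differ, for example because of availability, and each difference needs a documented reason. The record cannot be recreated after enrolment, so it must be in place before the first participant is randomised.

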### Participant timeline

3.4

The timeline of screening, enrolment, and interventions is provided in Table 3. The interventions will be provided at follow‐up visits taking place every 90 days. The baseline visit will include a neurologist's description of seizure history, including seizure semiology, epilepsy diagnosis, and etiology of epilepsy to the degree possible given resource limitations. Structured forms will be used. Several measures will be collected during follow‐up visits, including detailed seizure information, quality of life surveying, medication possession, stigma scale surveying using the Stigma Scale of Epilepsy (SSE),^26^ health visit history, school/work attendance, and injury surveying.

**TABLE 3 epi412889-tbl-0003:** Schedule of tests and events at each study visit.

	Screening	Baseline	90	180	270	360
Study visit		1	2	3	4	5
Informed consent	×					
Assess inclusion and exclusion criteria	×	×				
Medical history	×	×				×
Seizure diary		×	×	×	×	×
Concomitant medication history		×		×		×
Quality of Life in Epilepsy‐31 scale		×	×	×	×	×
Consumption and household assets module		×				×
Stigma Scale of Epilepsy		×	×	×	×	×
Medication possession ratio, as appropriate based on assigned arm			×	×	×	×
Health visit history (allopathic and traditional)		×	×	×	×	×
School/work attendance log		×	×	×	×	×
Injury survey		×	×	×	×	×
Status epilepticus query		×	×	×	×	×
Body weight, height, heart rate		×				×
Urine pregnancy test (for people of childbearing potential), *as needed	×	*	*	*	*	*
Clinical labs (including serum Na+, glucose), *as needed	*	×	*	*	*	*
Brain MRI	×					×
Conditional cash allocation, as appropriate based on assigned arm		×	×	×	×	×
Vitality status assessment			×	×	×	×

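### The 15 USD paid per 90-day visit is justified against a one-month drug price, so the claim that cash removes affordability as an explanation in the cash arm does not follow

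*Protocol article*

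**What the plan says.** Section 3.2 (Intervention description) makes the cash conditional on returning to the epilepsy clinic for "scheduled appointments (±7 days every 90 days"), and states: "Each visit for those in the CCT groups will entail the provision of 15 USD". It gives two price comparisons for the amount:

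- Transport: "it exceeds the general cost of transportation for a return visit in the area (~5 USD on average").
- Drug: the ASM "approximately costs ~4–10 USD for a monthly dosage in Guinea".

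From these it concludes that "this nudge will ensure participants in the CCT arm can afford the ASM, which enables study staff to assess outcomes from behavioral change", as opposed to affordability.

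Section 3.1 (Explanation for the choice of comparators) says what else the cash arm gets towards treatment: participants are "given an ASM recommendation and advice on purchasing ASMs". Free drug belongs to the other arm, and no further drug subsidy for the cash arm is described.

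Table 3 in section 3.4 has a row "Conditional cash allocation, as appropriate based on assigned arm", marked at baseline (study visit 1) and at days 90, 180, 270 and 360.

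**The concern.** The payment comes once per 90 days, but the drug price beside it is for one month. The conclusion about affordability needs both on the same time base.

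The sentence also does inferential work. It says outcomes in the cash arm can be taken as behavioural. Hypotheses 1b and 1c compare that arm with one where the drug is free. If the cash funds only part of the drug, lower ASM use or less seizure freedom in the cash arm could come from cost, from behaviour, or from both. Because the cash depends on attendance alone, good retention could also coexist with drug that was not bought.

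A smaller point bears on the same sums. Section 3.2 ties cash to return for follow-up visits, while Table 3 marks a payment at baseline. Without that payment, the first 90 days carry no cash at all.

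**Working it through.** **Inputs** (all from section 3.2 unless noted)

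- Payment: 15 USD per visit, every 90 days, taken as 3 months.
- Transport: 5 USD per return visit, taken as the full cost of the visit.
- ASM price: 4–10 USD per month.
- Payment dates: baseline, 90, 180, 270, 360 (Table 3), or the four return visits only (one reading of section 3.2).

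**Step 1. The plan's own comparison, on one month.** Transport + 1 × monthly price = 5 + 4 = 9 USD, up to 5 + 10 = 15 USD. Against 15 USD the comparison works, although at the top price the payment equals the cost and does not exceed it. So the stated justification is reproduced only when a single month of drug is counted.

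**Step 2. The same comparison over the 90 days between payments.** ASM = 3 × monthly price; total = ASM + 5.

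| ASM price per month | ASM, 90 days | With one trip | Shortfall with trip | 15 USD covers, with trip | 15 USD covers, ASM alone |
|---|---|---|---|---|---|
| 4 USD | 12 | 17 | 2 | 88% | 125% |
| 5 USD | 15 | 20 | 5 | 75% | 100% |
| 7 USD | 21 | 26 | 11 | 58% | 71% |
| 10 USD | 30 | 35 | 20 | 43% | 50% |

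Break-even prices:

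- ASM alone: 15 / 3 = 5 USD per month, inside the stated range.
- ASM plus transport: (15 − 5) / 3 = 3.33 USD per month, below the stated range.

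Using 90 / 30.44 months in place of 3 gives 16.8–34.6 USD with transport, which leads to the same conclusion.

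**Step 3. Over the year, counting costs and payments that fall before day 360.**

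- Need: 12 months of ASM plus three return trips (days 90, 180, 270) = 48 + 15 = 63 USD, up to 120 + 15 = 135 USD.
- Cash, with a baseline payment: 4 × 15 = 60 USD. The shortfall is 3–75 USD.
- Cash, without a baseline payment: 3 × 15 = 45 USD. The shortfall is 18–90 USD.

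**Step 4. Does the statistical plan depend on the affordability claim?** The sample size in section 6 rests on retention (Hypothesis 1a). The tests for 1b and 1c are one- and two-sample comparisons of proportions. None takes drug affordability as an input.

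**The case against.** **The sentence speaks of affording the ASM, not ASM plus transport.** This stands in part. A reader might infer that the cash never covers 90 days of drug. The stated prices do not support that, since at 4–5 USD per month it does. The shortfall holds at every price only once the trip is included. The protocol itself brings transport into the justification, and above 5 USD per month the drug alone is not covered.

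**A yearly total can be made to balance at the low end.** With all five Table 3 payments the cash is 75 USD, against 12 months of ASM plus four trips: 48 + 20 = 68 USD, up to 120 + 20 = 140 USD. That suffices up to (75 − 20) / 12 = 4.58 USD per month. So a shortfall at every price under any yearly accounting is not supported. But the fifth payment comes at day 360, when the treatment period is over. On the before-day-360 basis the gap remains, though it is only 3 USD at the lowest price with a baseline payment.

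**To afford is not the same as to be fully funded.** Table 1 gives adults in the prior cohort a mean household income per capita of 975 USD a year, about 244 USD per 90 days. A gap of 2–20 USD is roughly 1–8% of that, so many participants might top up. This is a fair limit on the practical size of the problem. It does not rescue the sentence, which says the cash itself ensures affordability. The figure is also a mean from a cohort in which 65% of adults were taking ASMs, whereas the trial enrols people off daily ASM for at least 30 days. The abstract itself names out-of-pocket ASM cost as a barrier.

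**The trial does not rest on this sentence.** Correct. A reader might infer that the comparison of arms, or the design, is undermined. It is not. Section 1.2 frames the aim as free ASMs against conditional cash, and the randomised contrast answers that. The primary outcome is attendance, for which 15 USD still exceeds transport. In Table 2 seizure freedom is secondary and ASM adherence exploratory.

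**Cost reasons may already be captured.** Section 1.2 plans structured and free-text documentation of barriers. Table 3 includes a consumption and household assets module at baseline and day 360, and a medication possession ratio at follow-up visits. The forms are not shown, so it cannot be said that cost is unrecorded. A possession ratio on its own, however, shows that supply is short, not why.

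**Section 3.2 may agree with Table 3 on baseline cash.** It also says cash is given at each visit, and Table 3 numbers baseline as visit 1. This is therefore an ambiguity to settle, smaller than the main point.

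**Conclusion.** The concern holds as a fault in the rationale and in the interpretation it licenses. On the protocol's own prices, 15 USD per 90 days is a partial subsidy: 43–88% of drug plus one trip, and enough for drug alone only in the lowest part of the price range. The statement that the cash ensures affordability, so that outcomes reflect behaviour, is not supported as written.

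The consequence is confined to how a cash-arm difference in ASM use (1b) or seizure freedom (1c) is explained. The randomised comparison of the two strategies, the attendance outcome and the sample size stand.

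The result assumes three months of drug per 90-day interval, that 5 USD is the full cost of a return visit, and that the cash arm receives no other drug subsidy. The protocol describes none. The arithmetic is secure. How often cost would in fact prevent purchase cannot be judged from the document.

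**What to change.** 1. Reconcile the payment, the visit interval and the monthly drug price in section 3.2 on one time base. The amount is the sponsor's decision, and none is proposed here.
2. If the figures stand, withdraw the statement on affordability and behavioural change, and interpret results for 1b and 1c as a partial cash subsidy plus attendance incentive versus free drug. The tests need no change.
3. Within the barrier documentation already planned at visits, make sure two things are recorded in the cash arm: months of ASM bought since the last visit, and cost as a reason for not obtaining it. If the existing forms already do this, say so.
4. Make section 3.2 and Table 3 agree on whether cash is paid at baseline and, if so, on what condition.

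The cost is a few sentences and one or two form items at existing visits. The downside is a narrower claim about mechanism.
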